### Analyses

#### Sample size, power, and effect size

To assess power for the primary outcome comparing the high- vs. low-intensity intervention at the discharge record level, we assumed the engagement rate in low-intensity hospitals will be 20% on average, and that hospitals in an intervention strategy group vary in their engagement proportion with a standard deviation (SD) of 0.15 on the logit scale (and a corresponding intraclass correlation coefficient of 0.0067 assuming logistic regression [51]). The standard deviation of 0.15 is based on Oregon and Massachusetts Medicaid data and is conservative for our purposes because the analysis will be stratified by site/hub and will adjust for baseline engagement rate, which will reduce variation between hospitals within strata, and this standard deviation does not account for those reductions. With 12 community hospitals per intervention arm and 100 patient discharges per community hospital, we have 85% power (two-sided test, alpha = 0.05) to detect a treatment effect with odds ratio of 1.45. Using the same assumptions as above, for a comparison of high- vs. low-intensity arms at the hospital level (i.e., no cluster effect which means interclass correlation coefficient is not different from zero) we have 97% power to detect a treatment effect with odds ratio of 1.45.

Baseline (prior to randomization) descriptive characteristics will be summarized by group, stratified by hub/state, at the community hospital level as well as at the participant discharge record level. Descriptive summaries of the distribution of continuous baseline variables will be presented with percentiles (median, 25th and 75th percentiles), and with mean and standard deviation. Categorical variables will be summarized in terms of frequencies and percentages.

#### Effectiveness analyses

The analysis of the primary outcome will be intention to treat based on randomized assignment and will compare high- and low-intensity arms using a mixed-effects logistic regression analysis. Hospitals that drop out of study participation will not be replaced and data will be tracked per randomized assignment. The main analysis model for the primary outcome will include hub as a hierarchical nested random effect with hospitals nested in the hubs. Observations are individual patient hospital discharges aggregated at hospital level, the primary outcome (derived from state Medicaid claims data) is patient MOUD engagement 34-days after hospital discharge (yes/no), the random effects are hubs and community hospitals, with hospitals nested within sites/hubs, and the fixed effect is strategy for MOUD engagement.

Analyses of secondary outcomes will have the same basic form as the primary analysis, with differences arising from the type of outcome (binary vs. interval-scaled vs. count) and from inclusion of further adjusters. Survival analysis techniques may be used for outcomes such as time to readmission or death [52]. 

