**MEASURES OF PRIMARY AND SECONDARY OUTCOMES**				
MOUD^a^ engagement 34 days post-discharge	X	X	X	X
ED^b^ visits or acute hospitalizations within 30 days post-discharge (OUD^c^ related or not)	X	X	X	X
Discharges against medical advice during index hospitalization	X	X	X	X

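### The power section promises adjustment for baseline engagement, but the primary model has strategy as its only fixed effect; the two sections specify different primary analyses

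*Protocol article*

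**What the plan says.** Two sections of the protocol article describe the primary analysis.

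- **Sample size, power, and effect size.** The between-hospital SD of 0.15 on the logit scale is called conservative because "the analysis will be stratified by site/hub and will adjust for baseline engagement rate", both of which would reduce variation between hospitals. The same sentence adds that the SD of 0.15 takes no credit for these reductions.
- **Effectiveness analyses.** The main model is a mixed-effects logistic regression. Its random effects are hub and community hospital, "with hospitals nested within sites/hubs, and the fixed effect is strategy for MOUD engagement". Further adjusters are mentioned only for the secondary outcomes.

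Table 1a lists "MOUD^a^ engagement 34 days post-discharge" for the pre-implementation period (the 12 months before randomization) as well as for the later periods. The hospital-level baseline value of the primary outcome will therefore be in hand.

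**The concern.** The model description does not merely omit a covariate list; it names the fixed effect, and there is one. The power section does not leave adjustment open; it commits to it. An analysis plan that follows either section contradicts the other.

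Two things are at stake. First, the adjusted and unadjusted analyses can fall on opposite sides of 0.05 in the same trial, and either could afterwards be called the one in the protocol. The Randomization section promises blinding of investigators during analysis only when possible, so the choice should not be left open. Second, there are only 12 hospitals per arm and randomization is stratified by hub alone, so nothing in the design balances baseline engagement between arms within a hub. Adjustment would give some protection if hospitals differ more than the assumed SD, which rests on data from two of the four states.

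**Working it through.** **Inputs from the sample-size section.** Low-intensity engagement 20%; odds ratio 1.45; 12 hospitals per arm with 100 discharges each; between-hospital SD 0.15 (logit); ICC 0.0067; two-sided alpha 0.05.

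**1. Reproduce the stated power.**
- High-intensity rate: odds 0.25 × 1.45 = 0.3625, so 0.3625/1.3625 = 26.6%.
- ICC: 0.15²/(0.15² + π²/3) = 0.0068, against 0.0067 stated; the difference is immaterial.
- Design effect: 1 + 99 × 0.0067 = 1.663. Effective size: 1200/1.663 = 721.5 per arm.
- Two-proportion power, 20% v 26.6%: **84.4%**, against 85% stated. With ICC 0 and 1200 per arm: 96.9%, against 97% stated.

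The stated figure thus comes from the full SD of 0.15, with no credit for baseline adjustment.

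**2. What adjustment would add.** This is a hospital-level calculation on the logit scale. Assumptions not in the document: 100 baseline discharges per hospital (in line with the recruitment average of 100 a year) and a correlation r of 0.5 to 0.8 between a hospital's true baseline and follow-up logits.
- Sampling variance of one hospital's logit: 1/(100 × 0.2 × 0.8) = 0.0625 in the low arm; 1/(100 × 0.266 × 0.734) = 0.0512 in the high arm.
- Unadjusted SE of the log odds ratio: √[(2·SD² + 0.0625 + 0.0512)/12]. At SD 0.15 this is 0.115, and ln(1.45)/0.115 = 0.3716/0.115 = 3.23.
- Reliability of the observed baseline: SD²/(SD² + 0.0625). R² = (reliability × r)². The adjusted SE is the unadjusted SE × √(1 − R²).
- Power from the noncentral t: 19 df unadjusted (24 hospitals less 4 hubs less strategy), 18 df adjusted.

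| SD | Reliability | R² (r = 0.5; 0.8) | Unadjusted | Adjusted, r = 0.5 | Adjusted, r = 0.8 |
|---|---|---|---|---|---|
| 0.15 | 0.26 | 0.02; 0.04 | 86.5% | 86.9% | 87.8% |
| 0.30 | 0.59 | 0.09; 0.22 | 62% | 65% | 72% |
| 0.40 | 0.72 | 0.13; 0.33 | 46% | 51% | 62% |

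The unadjusted 86.5% differs slightly from 84.4% because the method differs (logit-scale t test rather than design effect). The comparison that matters is along each row.

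**3. Simulation check.** Empirical logits, hub in the model, 6000 trials per setting.
- SD 0.15: about 86–87% unadjusted, and 85% (r = 0.5) or 86% (r = 0.8) adjusted, so no gain.
- SD 0.30: from 61% to 62% (r = 0.5) or 69% (r = 0.8).
- SD 0.40: from 45–46% to 48% or 59%.
- At r = 0.8 the two analyses disagreed on significance in about 5% of trials at SD 0.15, 17% at 0.30 and 23% at 0.40.

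**The case against.** The strongest reply is that nothing the protocol states numerically depends on the missing term. That stands. The 85% was computed without the reduction, and the protocol says so. The model as written is also valid: in a trial randomized within hubs, chance imbalance at baseline is not bias, and the hospital random effect carries it into the standard error. At the planned SD a baseline rate from about 100 discharges is mostly noise (reliability 0.26), so adjusting for it gains almost nothing.

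A reader might infer more: that the power claim collapses, or that the argument for a conservative SD fails altogether. The document supports neither. The SD argument has two grounds, and hub remains both as a randomization stratum and as a random effect in the model; only the baseline ground is missing. The larger gains come from SDs of 0.30 and 0.40 and from correlations that appear nowhere in the protocol. They show what adjustment would protect against, not that the SD of 0.15 is wrong.

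It can also be said that a journal article condenses, and that mentioning further adjusters for secondary outcomes implies that some already sit in the primary model. That reading is possible, but it does not outweigh an explicit list of terms with a single fixed effect. A full analysis plan may settle the matter; the article still makes two incompatible statements.

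**Conclusion.** The contradiction is real: one section commits to baseline adjustment and the section defining the model leaves it out. The stated power stands and the unadjusted analysis is valid, so the harm is ambiguity about the primary estimate, one lost ground for calling the SD conservative, and some forgone precision.

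That precision is worth about 0 to 1.3 points of power at the planned SD. It reaches roughly 3 to 16 points analytically at SDs of 0.30 to 0.40, and less in simulation. These larger figures rest on assumed SDs, an assumed correlation of 0.5 to 0.8, and 100 baseline discharges per hospital.

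Severity: should be fixed.

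**What to change.** In the Effectiveness analyses section, add to the primary model, as a fixed covariate, each hospital's 34-day MOUD engagement in the pre-implementation period (months -12 to -1), for example on the logit scale. The model then matches the sample-size section. Report the model without this covariate as a sensitivity analysis. State that the 85% power does not rely on the adjustment.

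The cost is a sentence of wording and one degree of freedom among 24 hospitals; the data are already scheduled in Table 1a. At the planned SD that degree of freedom and the noisy baseline may offset the gain, so the case for adjusting is protection against a larger SD and consistency with the protocol's own stated intent.

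Deleting the adjustment from the sample-size section, together with the part of the conservatism argument that rests on it, would also remove the contradiction, but it would give up that protection.

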#### Implementation analyses

Scores for AIM/IAM/FIM, OCM, CFIR inner setting measure, and Sustainability Tool will be calculated in accordance with published guidance and compared both across hospital groups and over time. The Sustainability Tool includes weighted factors with scores that are combined in an additive multi-attribute utility model [53] Analysis of the OCM uses a Bayesian model where a likelihood ratio is assigned to each possible response to each question. The likelihood ratios for the selected responses and the prior odds are multiplied together to yield *a posterior* odds, which can be averaged across the individual respondents. Group by time interaction analyses will be used to assess the association between changes in these measures through time and the primary and secondary quantitative outcomes.

The RE-AIM framework will be used to identify the reach of our implementation intervention, its efficacy, adoption, implementation, and maintenance, or sustainability [54]. This framework is well suited for randomized interventions in real-world settings.

#### Qualitative analyses

We will use a collaborative codebook development process involving a lead qualitative investigator and interviewers from each hub following an iterative, collaborative codebook development process [55, 56]. Parent- and sub- codes will relate to defined theoretical constructs (e.g., organizational readiness to change, resources, local environment, staffing models) and emergent topics identified in the data. After reaching consensus on final codes and definitions, we will apply codes to transcribed interview data using NVivo qualitative research management software (Lumivero, Denver, CO) in preparation for thematic analysis [57]. 

#### Economic analyses

The purpose of the economic evaluation will be to assess the value, in terms of both costs and effectiveness, of implementation support for HBOT in community hospitals. Here, costs, collected as resource use (e.g., personnel) rather than dollar amount spent, will consist of the costs of the different components of the provided implementation support. These costs will be divided into one-time setup costs and ongoing maintenance costs. Only maintenance costs will be used in calculating the efficiency of the implementation programs, as these are the costs that would be expended if the implementation programs were to be scaled up beyond the trial population. Resource use categories will consist of the time spent by hub staff providing training and support to community hospitals, as well as the time use of each local community hospital champion (for sites receiving the high-intensity intervention). Hub staff will document time spent on the preparation and delivery of each training session and will also document each supportive interaction with community hospitals, including approximate duration. The cost of personnel time will be estimated as the average total compensation for the appropriate job class. Effectiveness will be measured in terms of the change in proportion of patients engaged in MOUD at discharge and changes in post-discharge healthcare utilization (both acute care and hospital readmissions). The overall value of a given intensity of implementation support will then be measured in terms of the additional cost per additional unit increase in patients engaged in MOUD at discharge, and secondarily as the cost per acute healthcare visit averted and/or hospital readmission averted.

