### Outcomes

The primary outcome is “engagement with MOUD” measured as the proportion of community hospital OUD discharges engaged with MOUD within 34-days following hospital discharge during months 13–24 of the intervention. This outcome is adapted (to include those with a pre-existing OUD diagnosis) from the Healthcare Effectiveness Data and Information Set (HEDIS) Initiation and Engagement with Treatment (IET) measure used by more than 90% of health plans and specified by the National Committee on Quality Assurance (NCQA), making it relevant to how hospitals are rated and, potentially, reimbursed [30, 31, 38]. . Primary, secondary, and most exploratory outcomes will be derived from state Medicaid claims data (see Supplementary materials for specific claims codes that define these outcomes). Outcome measures are presented in Tables 1a and 1b.

**Table 1a Tab1:** Medicaid-based outcome measures

	Study Periods for Medicaid Data Abstraction (in months)			
	Pre-Implementation (-12 randomization (-1))	Implementation Year 1 (1–12)	Implementation Year 2 (13–24)	Post-Implementation (25–36*)

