While the hybrid type-2 design allows us to assess both patient level outcomes and compare implementation approaches in effecting these outcomes, there are limitations to our approach. While our intervention is designed such that hospitals can choose their preferred approach to HBOT, it likely does not provide an adequate level of support to facilitate the implementation of a well-functioning addiction consultation service. Patient level outcomes are based on state Medicaid claims data, which may not generalize to hospitalized patients with OUD covered through other mechanisms or in states without Medicaid expansion. Our mixed methods approach should also help us explain any difference (or lack thereof) in primary and secondary outcome measures between the intervention arms. Further, OUD diagnostic codes may not adequately capture all patients with OUD, those receiving MOUD while hospitalized, or those receiving MOUD following hospital discharge [58]. Importantly, claims do not capture patient preference or choice (e.g., some may be offered but decline MOUD). There are also several different approaches to implementation and our selection of practice facilitation using a program planning model cannot be compared to a conventional (i.e., top-down) planning model or other approaches [59]. We use four expert hubs working in parallel with a common set of HBOT materials for implementation support and, therefore, are not evaluating the use of a single centralized implementation support center. Most of our implementation outcomes are tracked using the RE-AIM framework and may not adequately capture external barriers and facilitators to implementation, although qualitative interviews will explore inner and outer contextual factors that could influence implementation processes or outcomes.

In summary, the development of national quality metrics related to engagement of hospitalized patients with substance use disorders, would indicate that there is consensus that HBOT is important. Yet, performance metrics alone have been insufficient in improving the management of OUD. For example, in 2004, initiation of and engagement in addiction treatment was 12% in Medicaid nationally; in 2016 it was still 12% [31]. Establishing effective implementation strategies for HBOT at community hospitals can drive translation and dissemination of HBOT nationwide while serving as a potential model for similarly addressing other substance use disorders.

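### The main cost-effectiveness ratio counts MOUD engagement at discharge, whereas the trial's effectiveness outcome is engagement within 34 days after discharge

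*Protocol article*

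**What the plan says.** The Economic analyses section names the effect: "Effectiveness will be measured in terms of the change in proportion of patients engaged in MOUD at discharge", together with changes in post-discharge healthcare use. It then expresses value as the "additional cost per additional unit increase in patients engaged in MOUD at discharge". Ratios based on utilization are given a lower rank: "secondarily as the cost per acute healthcare visit averted and/or hospital readmission averted". The at-discharge time point therefore appears twice, as the effect and as the unit of the main ratio.

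The rest of the article uses another time point:

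- **Outcomes:** the primary outcome is the proportion "engaged with MOUD within 34-days following hospital discharge during months 13–24 of the intervention".
- **Table 1a:** the corresponding claims measure is MOUD "engagement 34 days post-discharge".
- **Effectiveness analyses:** the modelled outcome "is patient MOUD engagement 34-days after hospital discharge (yes/no").
- **Abstract and Introduction:** the primary outcome and the hypothesis are both stated at 34 days.

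Study objectives and design lists cost-effectiveness of the high- against the low-intensity strategy among the matters to be explored.

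**The concern.** Under Economic analyses, the unit in which the high-intensity strategy is valued is not the unit in which it is tested. The article's own rationale separates the two states. The Introduction describes a gap between leaving hospital and entering treatment, and cites a study in which 39% of patients started on sublingual buprenorphine in hospital were engaged at 30 days. The primary objective concerns engagement after discharge.

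A ratio counted at discharge would credit patients who are later lost in that gap. A funder could not set the cost per engaged patient beside the primary result, because the two would count different patients. The conflict also leaves the denominator open: an analyst could defend either time point after seeing the data. The Discussion names policymakers and funders as the intended audience, and they are the natural readers of this ratio.

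**Working it through.** **1. Text comparison.** The 34-day time point is used in the Abstract, the Introduction's hypothesis, Outcomes, Table 1a and Effectiveness analyses. Engagement at discharge is used as an outcome only under Economic analyses. The nearest other items are MOUD initiation (exploratory, Table 1a) and the Abstract's mention of engagement at several time points. The article gives neither of them a time.

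**2. The plan's own figures.** The economic section gives no numbers, so the anchor is the design effect under Sample size, power, and effect size: control rate 20%, odds ratio 1.45, 12 hospitals per arm, 100 discharges each, ICC 0.0067, two-sided alpha 0.05.

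- High-intensity rate: odds 0.20/0.80 × 1.45 = 0.3625, and 0.3625/1.3625 = 26.6%. Difference d = 6.6 points.
- Design effect: 1 + 99 × 0.0067 = 1.663. Effective n per arm: 1200/1.663 = 721.
- Power = Φ[(d − 1.96·SE₀)/SE₁], with SE₀ from the pooled proportion and SE₁ unpooled. At n = 721 this is 84.4% (stated 85%). At n = 1200, without clustering, it is 96.9% (stated 97%).

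The stated power reproduces. It is power for the 34-day primary outcome and is not in question.

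**3. Illustration of the time-point difference.** Assumptions, none of them in the documents: everyone engaged at 34 days was engaged at discharge, and a share r of those engaged at discharge is still engaged at 34 days, equal in both arms. The difference at discharge is then d/r. For a given incremental cost, the cost per additional patient engaged at discharge is r times the cost per additional patient engaged at 34 days.

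| r | Difference at discharge (points) | Additional patients per 1,200 discharges | Cost per unit relative to 34 days |
|---|---|---|---|
| 0.39 | 16.9 | 203 | 39% |
| 0.5 | 13.2 | 159 | 50% |
| 0.7 | 9.4 | 113 | 70% |
| 0.9 | 7.3 | 88 | 90% |
| 1 | 6.6 | 79 | 100% |

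The value 0.39 is the Introduction's background figure. It concerns one drug, one cited study and 30 days, so it serves only as one end of a range.

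**4. What happens if retention differs by arm.** Take r = 0.9 in the high-intensity arm and 0.7 in the low-intensity arm, again purely as an assumption. The difference at discharge is 0.2661/0.9 − 0.20/0.7 = 0.2956 − 0.2857 = 0.0099, or 1.0 point (about 12 patients per 1,200). That is smaller than 6.6 points, so the at-discharge ratio would look less favourable (6.6/0.99 = about 6.7 times the cost per unit). The direction therefore depends on an assumption that the documents do not supply.

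**The case against.** The strongest reply is that the at-discharge wording is shorthand in a condensed article for an analysis the study only sets out to explore. An early outcome may also be deliberate, and the supplementary claims definitions, which are not shown here, may contain a measure close to it. Part of this stands. The article does not show that such a measure is uncollected, since MOUD initiation is listed for every study period and other engagement time points are mentioned. But this is not a detail left to a fuller document. The article states a specific measure twice, in a section of its own, and it conflicts with the trial's outcome. Either reading calls for a change of text.

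A reader might infer two further faults that the documents do not support:

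- **Weak capture of in-hospital treatment.** The Discussion concedes that codes may miss "those receiving MOUD while hospitalized, or those receiving MOUD following hospital discharge". That applies equally to the 34-day outcome and does not single out an at-discharge measure.
- **No between-arm contrast, because the effect is called a change.** The ratio is worded in additional cost per additional unit, and the objectives name the high- versus low-intensity comparison. The incremental intent is clear enough.

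**Conclusion.** The inconsistency is real and confined to the main cost-effectiveness ratio. Its effectiveness unit should be reconciled with the 34-day outcome before the economic analysis is run.

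Its numerical effect is not fixed by the documents. The 39% to 100% range rests on complete nesting of 34-day engagement within engagement at discharge and on equal retention in both arms. Equal retention is open to doubt in a trial of support meant to raise engagement after discharge.

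A reader might conclude that the ratio would value a weaker effect. No effect at discharge is given, and under equal retention the absolute difference there would be as large or larger. What can be said is that the endpoint is less durable. A reader might equally conclude that cost per engaged patient is understated 2.6-fold (1/0.39 = 2.56). That is only the far end of the illustrative range and not an estimate for this trial.

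The ratios per acute visit or readmission averted rest on a utilization outcome listed in Table 1a and stand as they are. The primary test and its power are untouched. As this is a non-primary analysis, severity is moderate to minor.

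**What to change.** In both sentences under Economic analyses, replace the at-discharge measure with MOUD engagement within 34 days after discharge, and state that the effect is the high-minus-low difference in that proportion.

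State the period over which costs and effects are counted, and make it the same for both. The primary outcome covers months 13–24, but support runs for 24 months and Table 1b places cost evaluation at months 12 and 24. Limiting effects to year 2 without limiting costs would create a new mismatch.

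If a separate at-discharge measure is intended, define it, name its data source, and report its ratio in addition to the 34-day one.

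For the 34-day ratio the cost is two wording changes and one sentence on the time window, with no new data. A separate at-discharge measure would also need its definition and source written down.
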